### Statistical methods

The main analysis will be logistic regression to test the main hypothesis related to the superiority of the MSTEP program based on a greater proportion of people making a clinically relevant gain in exercise capacity at 1 year. A secondary outcome will be the differences in proportions at 2 years also using logistic regression. The analysis will be based on intention-to-treat and all persons will be analysed in the groups to which they were randomized.

A secondary analysis will estimate the impact of exercise on the other relevant outcomes. For this approach, each outcome will be converted to a binary response variable based on published clinically meaningful changes (see Table 1) and generalized estimating equations (GEE) will be used to test the rate of response in the MSTEP program to the rate of response in the general guideline approach [85,86]. If there is a statistically significant effect of the intervention, then and only then, can the effects of the separate outcomes be interpreted as real [86].

The role of exercise engagement in explaining outcome variation will be estimated using multivariate modeling for both logistic and longitudinal growth models. A separate analysis will be conducted to examine relapse rate and other adverse events. All of these analyses will be adjusted for confounders using propensity scoring [27,87-89]. Factors used in the propensity score are: extent of complaints (co-ordination, weakness or heaviness in legs, anxiety/depression, bladder problems), presence of children, and exercise enjoyment at study entry [44]. Adjustment will also include age and sex and additional prognostic variables which improve model fit.

If people are unable to do the VO_2_peak test or the data from this test is aberrant (person did not reach a peak), we will use a validated a regression equation to estimate VO_2_peak measured in ml/kg/min from submaximal tests [46]. The equation, which is based on our pilot work on 60 subjects, is: VO_2peak_ = -11.83 + 1.78(Men) + 0. 2*each 10 meters distance walked in 6 minutes + 16.3 * L/min oxygen consumption estimated from the completed stage of step test.

As is consistent with policy from the funding agency, Canadian Institutes of Health Research (CIHR), we will conduct a gender-based analysis for exploratory purposes only. We will also explore whether people with different relapsing remitting type respond differently than people with progressive type of MS. This is accomplished by fitting an interaction term between group and gender and group and type of MS. A second sub-group analysis will explore the impact of the intervention among people with a different propensity to exercise. Propensity scoring permits exploration of this variable on outcomes through stratification by low, medium, and high values on propensity for exercise interest.

To minimize potential bias arising from missing data from missing assessments or losses to follow-up, multiple imputation [90,91] will be carried out on the longitudinal data for all outcomes with sufficient data. Imputation will be based on the data arising from key measured variables and values on the health questionnaires. As is usual, 80 imputed data sets are generated and 20 are chosen (to maximize dataset independence). Multiple imputation provides estimates of the value on a missing variable that would have been recorded if the person had been assessed. The estimated values incorporate the data that are available, cross-sectionally and over time, as well as variation in the multivariate distribution of this existing data. In the analysis, both the estimate and the associated error, within and between imputed data sets, are used and the model error term thus includes the usual sources of error as well as error arising from imputation. Without this process, the p-value tends to be underestimated and more likely to cross the conventional threshold for significance [90,91].

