**Methods/Design:**

The proposed study is an assessor-blind, parallel-group, randomized controlled trial (RCT). The duration of the intervention will be one year with follow-up to year two. The targeted outcomes are exercise capacity, functional ambulation, strength, and components of quality of life including frequency and intensity of fatigue symptoms, mood, global physical function, health perception, and objective measures of activity level. Logistic regression will be used to test the main hypothesis related to the superiority of the MSTEP program based on a greater proportion of people making a clinically relevant gain in exercise capacity at 1 year and at 2 years, using an intention-to-treat approach. Sample size will be 240 (120 per group).

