### Objectives

The global aim of this study is to contribute evidence for the role of targeted exercise in altering MS outcomes over time. The primary research question is to what extent does an MS Tailored Exercise Program (MSTEP) result in greater improvements in exercise capacity and related outcomes over a one year period in comparison to a program based on general guidelines for exercise among people with MS who are sedentary and wish to engage in exercise as part of MS self-management. The primary outcome for this question is exercise capacity measured using cycle ergometry. However exercise efficiency, functional ambulation, strength, components of quality of life including frequency and intensity of fatigue symptoms, mood, global physical function, and health perception will also be measured as components of a global response outcome. The first confirmatory hypothesis is that MSTEP will result in a greater proportion of people making clinically relevant gains (at least 10% change) in exercise capacity than with general guidelines after 12 months of intervention; a secondary hypothesis is that, while there may be some decline in exercise capacity among individuals from end of intervention to follow-up one year later, the decline will be greater in the general guideline group augmenting the difference between groups in the proportion making 10% change from study entry to 24 months. In other words, gains will be maintained more for the MSTEP group over the general guideline group.

An exploratory hypothesis is that more of the targeted outcomes will improve with the MSTEP program than the general guideline approach. An explanatory hypothesis is that these gains will be accompanied by reports of greater exercise self-efficacy (confidence) with the MSTEP program than with the general guideline program leading to more consistent exercise engagement and improved long-term adherence.

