### Sample size

Sample size is based on a test of proportions. Assuming a range of response proportions in the General Guideline Group of 0.2 to 0.5, we have powered this study at 80% to detect a relative risk of >1.5 in favour of the MSTEP Group (Type I error 0.05). A sample size of 120 per group (total sample size of 240) is targeted.

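### The secondary hypothesis predicts less decline and a widening gap after month 12, but the planned 24-month comparison cannot separate widening from mere persistence

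*Protocol article*

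**What the plan says.** The Objectives section gives one confirmatory hypothesis, at 12 months: "MSTEP will result in a greater proportion of people making clinically relevant gains (at least 10% change) in exercise capacity" than the general guidelines. It then gives a secondary hypothesis about what follows, with the response assessed at month 24: "the decline will be greater in the general guideline group augmenting the difference between groups in the proportion making 10% change from study entry". It restates this as "gains will be maintained more for the MSTEP group over the general guideline group".

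Statistical methods gives the matching analysis as "A secondary outcome will be the differences in proportions at 2 years also using logistic regression". The abstract (Methods/Design) is to the same effect, naming superiority on a "greater proportion of people making a clinically relevant gain in exercise capacity at 1 year and at 2 years".

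The other models in Statistical methods have other jobs:
- The GEE tests the global response across the other outcomes.
- The growth models serve exercise engagement: "The role of exercise engagement in explaining outcome variation will be estimated using multivariate modeling for both logistic and longitudinal growth models".
- The interaction terms are group by gender and group by type of MS.

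Nothing compares the 24-month difference with the 12-month difference.

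**The concern.** Greater decline, a larger difference and better maintenance are all statements relative to month 12. The planned test uses only the responder status at month 24. Any difference already present at month 12 carries forward into it, and the primary hypothesis expects such a difference.

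A significant 24-month result is therefore compatible with a gap that widened, stayed the same or partly closed. A non-significant one is compatible with a small gap that grew. Reading that single test as evidence on maintenance would credit MSTEP with a property that the analysis did not examine.

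**Working it through.** **Inputs.** 120 per group, Type I error 0.05 and relative risk 1.5 (Sample size). The control response is given only as a range: "Assuming a range of response proportions in the General Guideline Group of 0.2 to 0.5". Two-sided testing, the 12- and 24-month rates and the within-person correlation are assumptions, because the protocol does not state them. No dropout is allowed for.

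**1. The plan's own power, which is also the chance that mere persistence is significant.** With n per group, control rate c, MSTEP rate t and p̄ = (c + t)/2:

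power = Φ{ [(t − c) − 1.96·√(2p̄(1 − p̄)/n)] / √([c(1 − c) + t(1 − t)]/n) }

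For c = 0.40, t = 0.60, n = 120: √(2 × 0.25/120) = 0.0645 and √(0.48/120) = 0.0632. Then (0.200 − 0.1265)/0.0632 = 1.16, and Φ(1.16) = 0.88.

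If a relative risk of 1.5 is present at month 12 and unchanged at month 24, with no decline in either group, the 24-month test is significant with these probabilities:

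| Control rate | 0.20 | 0.30 | 0.35 | 0.40 | 0.50 |
|---|---|---|---|---|---|
| Probability | 0.43 | 0.67 | 0.78 | 0.88 | 0.98 |

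The stated 80% for a relative risk of 1.5 is thus reached only from a control rate slightly above 0.35. That is a separate matter, and this point does not depend on it.

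**2. Cases where the hypothesis is false** (control/MSTEP rates, 120 per group):

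| Month 12 | Month 24 | Difference | Relative risk | Odds ratio | P(24-month test significant) |
|---|---|---|---|---|---|
| 0.40/0.60 | 0.40/0.60 | 0.20 → 0.20 | 1.50 → 1.50 | 2.25 → 2.25 | 0.88 |
| 0.50/0.75 | 0.45/0.65 | 0.25 → 0.20 | 1.50 → 1.44 | 3.00 → 2.27 | 0.88 |
| 0.40/0.60 | 0.30/0.50 | 0.20 → 0.20 | 1.50 → 1.67 | 2.25 → 2.33 | 0.89 |

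In the first row nothing declines. In the second the gap shrinks on every scale. In the third both groups lose 10 points, so the hypothesis is false on the absolute scale only.

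In simulation (10,000 trials, latent-normal within-person correlation 0.5 or 0.8), a contrast of the change in proportion wrongly declared widening in about 2% of trials in the first and third rows. The second row was not simulated.

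**3. The reverse case.** Let the gap grow from 5 points (45% vs 40%) to 10 points (48/120 vs 36/120). At month 24 the pooled proportion is 84/240 = 0.35 and the standard error is √(0.35 × 0.65 × 2/120) = 0.0616. So z = 0.10/0.0616 = 1.62 and p = 0.10: the gap doubled and the test is not significant.

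**4. Precision of the contrast that would answer the question.** With p(1 − p) ≈ 0.24 at each time and within-person correlation ρ:

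SE = √(2 groups × 2 × 0.24 × (1 − ρ)/120)

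- ρ = 0.3: SE 0.075, 95% CI ±14.7 points
- ρ = 0.5: SE 0.063, ±12.4 points
- ρ = 0.7: SE 0.049, ±9.6 points

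Simulated power is about 0.11 to 0.14 for widening from 20 to 25 points (0.40/0.60 to 0.30/0.55), and about 0.29 to 0.41 for widening from 20 to 30 points (to 0.25/0.55).

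**The case against.** **The 24-month comparison is relevant.** The hypothesis is worded through the proportion with a 10% change from entry to 24 months, and that is the variable analysed. This stands in part: the test answers whether a benefit is present at 24 months. It does not answer whether the gap grew.

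**Nobody has said the result will be reported as maintenance.** This stands. A reader might infer that a significant 24-month test will be announced as better maintenance. The protocol gives no such decision rule, so the claim is only that it could be misread that way. Both proportions will be available, but setting them side by side gives no interval that allows for within-person correlation.

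**Any shrinking absolute gap proves the point.** A reader might take a fall from 50% vs 33.3% to 40% vs 25% as plain refutation of the hypothesis, because the gap goes from 16.7 to 15.0 points while the 24-month test gives p = 0.013. That reading is too strong. The odds ratio is 2.0 at both times and the relative risk rises from 1.5 to 1.6. The Objectives wording favours the absolute scale but does not name one, so the argument should rest on cases that fail on every scale.

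**The responder contrast is only a proxy for decline.** The Objectives also speak of individuals losing exercise capacity, a within-person change in VO2peak. This stands: a contrast of responder proportions addresses the widening and only indirectly the decline.

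**Model detail belongs in the analysis plan.** It often does. Here, however, the article states both the hypothesis and its year-2 test, and the two do not match.

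**Conclusion.** The point holds as a mismatch between a stated secondary hypothesis and its stated test. If a 12-month difference of 0.60 versus 0.40 merely persists, the 24-month test is significant with probability about 0.88. Over the protocol's control range, with a relative risk of 1.5, that probability runs from 0.43 to 0.98. These figures assume two-sided testing, complete data and illustrative rates; the logical gap does not depend on them.

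The documents do not support going further. The 24-month comparison is valid for persistence of benefit, and the primary 12-month analysis is untouched. The correction should be made, but it concerns a secondary claim and the trial has little power to settle it.

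**What to change.** Choose one of two routes.

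1. **Keep the hypothesis and add its contrast.** Analyse the 12- and 24-month responses jointly, for example by a repeated-measures GEE with group, time and group-by-time. Base any maintenance statement on the difference between groups in change of response proportion, with a 95% confidence interval. Obtain it on the absolute scale, by identity link or marginal standardisation. A logit interaction is a ratio of odds ratios and can give a different answer: it is exactly null in the 50%/33.3% to 40%/25% case above. Report the 24-month difference separately, as persistence of benefit.
2. **Restate the secondary hypothesis** as superiority at 24 months, and make no claim about decline or widening.

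The first route costs one model and some wording, on VO2peak responses that the plan already needs at both times. Its drawback is the imprecision shown above, so the contrast should be presented as an estimate and not as a powered test. The second costs only wording, but gives up the question of maintenance.

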### Secondary outomes

A second primary effectiveness outcome will be a global test based on creating binary response variables for all relevant outcomes using known clinically meaningful change to indicate response (or ½ SD if this is not known [82]) (see Table 1).

Adherence and exercise engagement will be monitored using a combination of exercise diaries and accelerometers. The exercise diaries are a good short-term method and also serve as a way for the participants to track their progress as well as any symptom changes (positive or negative) such as fatigue or pain. We will use daily diaries for the first 3 months and subsequently ask people to complete a diary and wear an accelerometer for one of the weeks in the month preceding their scheduled assessment. The weeks for the diary and for the accelerometer will not coincide.

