All secondary outcomes will be analysed using a global response statistic. A challenge with trials of complex interventions particularly those which tailor the intervention to patient needs, which typify rehabilitation-type interventions, is that no one outcome is likely to capture the effect equally for each person and analysing each outcome separately is often considered suspect in some research cultures. Recently in a 2009 publication in the Archives of Physical Medicine and Rehabilitation, Bagiella [85] demonstrates the value of using modern statistical methods to combine multiple outcomes into a composite response variable. We have demonstrated the benefit of this approach in evaluating a case-management intervention for people discharged home post-stroke [95].

We will also use propensity scoring, a widely used epidemiologic method to improve validity and precision when there is a need to consider multiple confounders that also may be correlated; a propensity score is calculated for each person based on their probability of taking an action or treatment, here engaging in exercise. Using this method, the propensity score is the adjustment variable, either as a continuous variable or a categorical variable such as quintiles (depending on linearity). The advantage is that multiple confounders can be combined in a single propensity score; adjustment in the analysis for the single propensity score also adjusts for all the confounders summarized in the score [89].

The results of the trial will contribute needed evidence for the development of guidelines for exercise for MS. If proven effective, the content will be made available at no cost.

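### A significant global GEE test is made sufficient to call the separate outcomes real, but it does not control false claims on individual components once some of them respond

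*Protocol article*

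**What the plan says.** In Statistical methods, every outcome other than VO2peak becomes a binary response at its Table 1 threshold, and "generalized estimating equations (GEE) will be used to test the rate of response in the MSTEP program to the rate of response" in the control group. The rule for the individual outcomes follows: if the intervention effect is statistically significant, "then and only then, can the effects of the separate outcomes be interpreted as real". The Discussion repeats the approach: "All secondary outcomes will be analysed using a global response statistic".

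The status of this analysis varies within the article. The section on secondary outcomes says "A second primary effectiveness outcome will be a global test based on creating binary response variables for all relevant outcomes". Statistical methods calls it a secondary analysis. Objectives says "An exploratory hypothesis is that more of the targeted outcomes will improve with the MSTEP program than the general guideline approach".

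The article states no significance level, test or multiplicity adjustment for the separate outcomes. The only Type I error, 0.05, is in the Sample size paragraph.

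**The concern.** The quoted rule has two halves. *Only then* makes a significant global test necessary, which is harmless. *Then* makes it sufficient, which is a statistical error. Rejecting the global null supports the statement that at least one component differs. It does not support a statement about any particular component.

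This matters because the components are diverse: cycling efficiency, step test, walking, strength, fatigue, mood, physical function, health perception and quality of life. An effect on some and not on others is plausible. The Discussion itself says that no single outcome is likely to capture the effect equally for everyone. A true effect on a few fitness items could open the gate, and a chance difference on fatigue or mood would then be reported as real. The Discussion says the results are meant to feed into exercise guidelines for MS.

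**Working it through.** **Plan's own figure.** There is none to reproduce, because the article gives no error rate for the component outcomes.

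**Number of components** (Table 1, components of the global outcome).
- By construct: efficiency, sub-maximal capacity, ambulation, strength, fatigue, mood, physical function, health perception, quality of life = 9.
- By measure with a stated threshold: efficiency 3 + step test 1 + walk distance 1 + strength 4 + fatigue 1 + mood 1 + physical function 1 + health perception 1 + quality of life 1 = 14.
- The fatigability index would be a fifteenth, but Table 1 gives it no change threshold.

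**Simple bound.** If the gate is certain to open and *m* null components are independent and tested at two-sided 0.05, P(at least one false claim) = 1 − 0.95^*m*. For claims favouring MSTEP only it is 1 − 0.975^*m*.

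| *m* null | either direction | favouring MSTEP |
|---|---|---|
| 5 | 22.6% | 11.9% |
| 7 | 30.2% | 16.2% |
| 10 | 40.1% | 22.4% |

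Correlation between components and a gate that sometimes stays shut both lower these figures, so they were simulated.

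**Simulation inputs.**
- From the article: 120 per arm.
- Assumed: control response 0.30 (inside the 0.2 to 0.5 range of the Sample size paragraph); odds ratio 2 on affected components; exchangeable latent-normal correlation 0.1, 0.3 or 0.5; unadjusted two-sided 0.05 component tests.
- An odds ratio of 2 at 0.30 gives odds 2 × 0.30/0.70 = 0.857, a rate of 0.857/1.857 = 0.46 and a relative risk of 0.46/0.30 = 1.54. This is close to the article's design effect: "we have powered this study at 80% to detect a relative risk of >1.5".
- Global test: z-test on the mean responder rate, equivalent to a common-effect GEE with independence working correlation and robust variance.
- Event counted: global test significant **and** at least one truly null component significant.

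**Results, 15 components.**

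| affected | either direction, correlation 0.1 / 0.3 | favouring MSTEP, correlation 0.1 / 0.3 / 0.5 |
|---|---|---|
| 0 | 4–5% | – |
| 5 | 27 / 19% | 20 / 15 / 15% |
| 7 | 31 / 21% | 18 / 15 / 14% |
| 10 | 23 / 19% | 11 / 12 / 11% |

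At correlation 0.5 the either-direction rate is about 14–15%. Repeat runs put the mixed cases at roughly 14–29% in either direction and 10–21% favouring MSTEP. The setting with seven of 15 affected at correlation 0.1 is the highest, at about 31%. With 14 components the figures are slightly lower.

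**Results, 9 components, some affected.** Roughly 8–17% in either direction and about 7–12% favouring MSTEP.

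**Wider assumptions** (relative risk 1.5 or 2.0, correlation 0 to 0.5). With 3 to 12 of 15 affected: 10–45%. With 3 to 7 of 9 affected: 7–27%. Favouring MSTEP only: about 6–27% and 5–14%.

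**After the fix.** With Holm across all components behind the gate, the same wide grid gives 1–5%. The highest value, 5.2%, is within simulation error: with 3,000 trials the standard error at 5% is √(0.05 × 0.95/3000) = 0.4 points.

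**The case against.** The strongest reply is that the article does not say components will be tested unadjusted at 0.05. How they are tested after the gate is commonly left to an analysis plan, which is not shown. A reader might infer that unadjusted testing is prescribed; the text does not support that, and the percentages are conditional on it. What stands is that the article does not leave the matter open. It states that a significant global test is enough, and that statement is wrong whatever tests follow.

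Second, Objectives labels the component-level hypothesis exploratory, and the only hypothesis called confirmatory at 12 months is VO2peak. Strict family-wise control over exploratory outcomes is not obligatory. This lowers the stakes, but the label conflicts with calling component effects real and calling the global test a second primary outcome. If exploratory is meant, the sentence still has to change.

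Third, a reader might conclude that the gate gives no protection, or that the false-claim risk is 20–30% over 15 tests. Neither holds. When no component is affected the error stays at or below about 5%. Fifteen is the largest count and includes an index without a threshold. Any single percentage depends on correlation, effect size and number of nulls, none of which is given. The three efficiencies share a numerator, so low correlation among them is unlikely. If the worry is false claims of benefit, the one-directional figures are the relevant ones, and they are lower.

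**Conclusion.** The point holds as a flaw in a stated inference rule. The global test controls component error only in the weak sense, that is, when nothing is affected. In mixed situations the individual claims are not controlled. Under the stated assumptions the excess over a nominal 5% is moderate with 9 components and up to several-fold with 14 or 15. The direction of the conclusion does not depend on the exact figures; its size does. A reader might also infer that the main trial result is compromised. It is not: the VO2peak responder comparison is a separate logistic regression and does not use this rule.

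**What to change.** Replace the sentence in Statistical methods with: *If the global test is significant, the separate outcomes are tested with Holm adjustment across the pre-listed Table 1 components (list fixed before unblinding), and only adjusted p<0.05 is claimed; otherwise component effects are reported as estimates with confidence intervals, without confirmatory claims.*

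The list must say whether it has 9, 14 or 15 members, since the adjusted p-values depend on it; including the fatigability index would require a threshold. Holm controls the family-wise error without the gate, so keeping the gate is a choice that costs some power.

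If the components are meant as exploratory, say so, report estimates with confidence intervals only, and delete the statement that their effects can be interpreted as real. In either case, give the global test one status throughout the article.

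The cost is a sentence and a standard p-value adjustment. Data collection and sample size do not change. The downside is that fewer individual components will reach significance.

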## Discussion

The MS community is looking for interventions to help alleviate the disabling sequelae of MS. Exercise is a well-known intervention which has known benefits to all, it has no negative side effects when prescribed appropriately, it has other benefits beyond disability such as reducing obesity and cardiovascular risk. It is hypothesized to have neurorehabiliative effects [15] and it is an intervention that is accessible to all at little cost. Yet, few exercise regularly. For people with MS, our survey of exercise barriers [44] showed that a major barrier was in not knowing what to do, being afraid of heat exhaustion, and fatigue. Proper instruction and tailoring exercise to specific needs could overcome these barriers.

The exercise program is novel. It incorporates all elements of the “Activity Pyramid” [92]: lifestyle activity; aerobic activity, strength and flexibility. It incorporates the notion of a “push-day” when persons are encouraged to push themselves to exercise intensely for short bursts. It is designed to add some form of exercise to most days.

In addition, this trial incorporates a number of statistical approaches rarely applied in the rehabilitation field, yet this field typically conducts research that would benefit from more modern statistical and methodological approaches.

The primary outcome is binary not a difference of two means. This is a more interpretable outcome and facilitates knowledge translation as people with MS and their care providers can readily understand what proportion of people made a relevant gain, whereas a mean difference may not apply to individual subjects. This outcome permits a calculation of number-needed-to-treat (NNT) [93], a very useful statistic in terms on comparative effectiveness [94]. With this outcome, it is also possible for research results to present data showing factors increasing the probability of a positive response permitting participants and providers alike to identify whether an individual is in a group more or less likely to benefit and perhaps provide additional interventions to increase probability of response.

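### For the propensity-to-exercise subgroup the protocol states only stratification, not the group-by-factor interaction it gives for gender and MS type

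*Protocol article*

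**What the plan says.** Under Methods, Statistical methods, the protocol article describes three subgroup analyses. For gender and type of MS it gives the method: "This is accomplished by fitting an interaction term between group and gender and group and type of MS". It then adds: "A second sub-group analysis will explore the impact of the intervention among people with a different propensity to exercise". The method stated for that one is different: "Propensity scoring permits exploration of this variable on outcomes through stratification by low, medium, and high values on propensity for exercise interest". No group-by-propensity term is named, and no cut-points or stratum sizes are given.

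The Discussion defends the binary primary outcome partly because it makes it possible to present "data showing factors increasing the probability of a positive response", and describes this as "permitting participants and providers alike to identify whether an individual is in a group more or less likely to benefit".

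**The concern.** The question in a subgroup analysis of a treatment effect is whether that effect differs between subgroups. A group-by-factor interaction answers it. Splitting the sample into low, medium and high gives three smaller comparisons and no test of the difference between them. If the three are then compared by which reached significance, chance and low power alone can look like a subgroup effect.

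This subgroup lies close to the trial's rationale. The Background argues that a program must engage people who do not exercise, so readers are likely to look at this result when deciding who should be offered MSTEP.

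The Discussion has a related looseness. Both arms receive an exercise program. A factor that raises the chance of a 10% VO2peak gain in both arms is prognostic. It does not show who gains more from MSTEP than from the general guidelines.

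**Working it through.** **Inputs from the protocol article (Sample size; Trial design).** Control response: "Assuming a range of response proportions in the General Guideline Group of 0.2 to 0.5". Effect: "we have powered this study at 80% to detect a relative risk of >1.5 in favour of the MSTEP Group". Alpha: "Type I error 0.05". Target 120 per group, allocated 1:1.

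**Assumptions (not in the document).** Equal thirds balanced by arm, so 240/3 = 80 per stratum and 40 per arm; complete outcomes; a two-sided 5% test; separate reading of each stratum by significance.

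**Step 1: the plan's own figure.** With control rate p1, p2 = 1.5·p1, d = p2 − p1 and p̄ = (p1 + p2)/2:

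power = Φ{[d√n − 1.96√(2p̄(1−p̄))] / √(p1(1−p1) + p2(1−p2))}

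At n = 120 per group, power is 43%, 67%, 88% and 98% for p1 = 0.2, 0.3, 0.4 and 0.5. The size needed for 80% is 294, 163, 97 and 58 per group. So 120 matches RR 1.5 only near p1 = 0.36 and does not reproduce across the stated range. That is a separate matter; here it only shows that the formula is on the plan's terms.

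**Step 2: power in one stratum, n = 40 per arm.** Example at p1 = 0.3, p2 = 0.45: d√n = 0.15 × 6.325 = 0.949; 1.96√(2 × 0.375 × 0.625) = 1.342; denominator √(0.21 + 0.2475) = 0.676; Φ(−0.58) = 0.28.

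**Step 3: three strata with the same true RR of 1.5.** With stratum power w, all three are significant with probability w³, none with (1−w)³, and the pattern is mixed with 1 − w³ − (1−w)³. The last two columns come from 100,000 simulated trials per row. The interaction test is a 2-df heterogeneity test of the log odds ratios.

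| Control rate | w | All | None | Mixed (formula) | Mixed (simulated) | Interaction test flags |
|---|---|---|---|---|---|---|
| 0.2 | 17.5% | 0.5% | 56% | 43% | 44% | 3.9% |
| 0.3 | 28% | 2% | 37% | 61% | 61% | 4.4% |
| 0.4 | 43% | 8% | 18% | 74% | 74% | 4.6% |
| 0.5 | 64% | 26% | 5% | 69% | 69% | 4.4% |

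With no effect in any stratum, at least one is significant in 1 − 0.95³ = 14% of trials.

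**Step 4: control rates that differ by stratum.** A score built on exercise-related factors may well track response. With RR 1.5 throughout and control rates 0.2/0.3/0.4, the mixed pattern appears in 66% and the interaction test flags 5.6%. With 0.2/0.35/0.5 the figures are 78% and 9.6%. The second is above 5% because a constant RR is not a constant odds ratio: (0.3/0.7)/(0.2/0.8) = 1.71, (0.525/0.475)/(0.35/0.65) = 2.05, (0.75/0.25)/(0.5/0.5) = 3.00. With a constant odds ratio of 2.05 at the same control rates, the interaction test flags 4.4%.

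**Step 5: what the interaction can resolve.** At 0.3 v 0.45 the variance of a stratum log odds ratio is 1/12 + 1/28 + 1/18 + 1/22 = 0.220. The difference between two strata has SE √(2 × 0.220) = 0.663, so the ratio of two odds ratios must reach about exp(1.96 × 0.663) = 3.7 to be significant. The test is honest but weak.

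**The case against.** The strongest reply is that the article is condensed, the analysis plan is not shown, and stratifying a score into three levels is compatible with a group-by-stratum term. The sentences just before show that the authors know the method. A reader might infer that an interaction test is excluded, or that significance will be judged within each stratum. The text says neither, and neither should be claimed. What remains is that a method is stated for this factor, it differs from the one stated for the other two, and it does not by itself answer the question asked.

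Second, the size rests on assumed equal thirds and an assumed reading rule. A reader might also infer that a uniform effect would usually look mixed. At a control rate of 0.2 that fails: no significant stratum (56%) is likelier than a mixed pattern.

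Third, a reader might infer that the propensity analysis is not offered as exploratory, because the explicit restriction is attached to gender. The same paragraph uses the language of exploration for all three analyses, so that reading does not stand.

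Fourth, the Discussion wording is hedged, serves as rationale for a binary outcome, and is not tied to the propensity strata. It does not say that individuals will be told whether they will benefit. Offering extra help to people unlikely to respond is also a legitimate use of prognostic information. What stands is only that it treats predicting response as if it were predicting benefit.

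**Conclusion.** The point holds in a limited form. The stated method for the propensity subgroup does not test effect modification, unlike the method for gender and MS type. If the strata were read separately, a uniform RR of 1.5 would give a mixed pattern in about 44% to 74% of trials when control rates are equal across strata. An interaction test flags about 4% to 5%, rising to about 9% to 10% on the odds-ratio scale if control rates run from 0.2 to 0.5 across strata. These figures assume equal thirds, 40 per arm, complete data and a two-sided 5% reading in each stratum.

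The primary analysis is untouched. The consequence is confined to an exploratory subgroup and to one Discussion sentence, but the correction costs almost nothing and makes the three subgroup analyses consistent.

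**What to change.** - In Statistical methods, fit a group-by-propensity interaction in the logistic model, as for gender and MS type. Enter the score as continuous or as a trend over thirds; the Discussion already allows a continuous score when it is used for adjustment.
- Show stratum-specific effects with 95% confidence intervals only beside the interaction estimate and its interval.
- State the effect scale. A logistic interaction concerns odds ratios, whereas the sample size is set in relative risks, and the two can disagree when control rates differ by stratum.
- In the Discussion, limit statements about who is more or less likely to benefit from MSTEP to group-by-factor interactions, and call factors that predict response in both arms prognostic.

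The cost is one model term and a few sentences, with no new data. The downside is small: the interaction test has low power, so the trial will be able to say less about this subgroup.
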